#### Data Analysis and Integration

Data will be analyzed using several methods. Specifically, instances of nonverbal behavior displayed by the learner and the virtual human will be coded, and dyadic data analyses will be carried out to examine the extent to which the learner mirrored the behavior of the virtual humans. Then, interactions using the RIAS and FACS will be coded. Another aspect that will be investigated is how participants responded to each virtual human after their action review by using the feedback in their second attempt at the scenario. Thus, it is necessary to test the relationship between the nonverbal behavior the learner demonstrated, and the assessment scores focused on that behavior (ie, if a learner demonstrates nonverbal behavior through the scenario, do the assessments detect it?). These will be tested in a structural equation model that will be compared to the qualitative data.

Importantly, analyzing video and individual-level data will help explain the extent to which participants followed instructions regarding nonverbal behavior and connect it to communication skills outcomes. The R-squared of nonverbal behavior relative to verbal behavior by learners on the OSCE outcome will be calculated to guide virtual human simulations. Data will be integrated by merging the qualitative and quantitative data, which will yield new insight into the particular mechanisms of nonverbal behaviors related to OSCE outcomes. Integration aims to generate meta-inferences, that is, integrated conclusions, beyond what either database alone could determine. The outcomes will provide a better understanding of human-computer interaction with virtual humans, which will inform future informatics interventions and identification of variables to assess nonverbal communication for inclusion in the virtual human.

### Exploratory Sequential Design

#### Overview

To develop a new conceptual model of nonverbal communication to inform virtual human-based training (aim 2) and develop new nonverbal functionality into the MPathic-VR virtual human simulation by creating an automated nonverbal communication behavior assessment for health care providers (aim 3), an exploratory sequential design will be carried out. First, a qualitative study using grounded theory methods [49] will be conducted to explore patient-provider communication, in addition to drawing from existing models. The follow-up quantitative strand will assess how well the system detects added features of nonverbal behavior through a quality control check.

#### Data Collection

For the qualitative grounded theory phase of this exploratory sequential design, data sources will include findings and video data from the MPathic-VR trial (aim 1). Interviews will also be conducted with providers focused on understanding intentional nonverbal communication (eg, mirroring, silence, distance, smiling, nodding, and leaning). Specifically, using theoretical, purposeful sampling [49] of providers (eg, physicians, nurse practitioners, and physician assistants) actively seeing oncology patients, 20 providers will be recruited from the University of Michigan health system, seeking variation in terms of cancer specialty, years since training, gender, and other demographics. The ultimate sample size will be determined by data saturation—the point at which the theory is developed, and new information is not emerging [50]. It is necessary to obtain the providers’ perspectives firsthand of intentional nonverbal communication to develop a patient-centered model. The quantitative strand will consist of video recordings that will allow for comparisons of nonverbal behaviors from provider participants between the system-recorded (Kinect) responses and manually scored records.

#### Data Analysis and Integration

Patient-provider interviews will be analyzed following Corbin and Strauss’ [49] constant comparative method, including open and focused coding, to develop a theory of the process of patient-provider nonverbal communication. This model will provide a theoretical basis for the subsequent automated nonverbal communication behavior assessment I will develop. The outcomes will be a new model of nonverbal communication that refines models of patient-centered communication and novel nonverbal elements to include in MPathic-VR for testing.

The qualitative data analysis, including coding of nonverbal behavior, provider interviews, and the FACS and RIAS models of communication assessment, will inform the development of a novel automated nonverbal communication behavior assessment that will be tested. Specifically, qualitative findings will be incorporated using building integration to systematically use the qualitative findings to develop the assessment. Themes will inform assessment features, and qualitative codes will inform variables to measure in the automated nonverbal communication behavior assessment [51]. The video recordings will be used to assess the reliability of the assessment by calculating Cronbach α using .8 as a standard for internal consistency and will be compared with OSCE nonverbal behavior ratings to gather initial evidence of construct validity. Finally, the manually coded video data will be compared to the Kinect sensor data, both dichotomously scored for each encounter, to gather further evidence of the validity of the assessment. As described above, this existing nonverbal data recorded whether or not 4 nonverbal behaviors (eg, smiles, nods, body lean, and eyebrow raises) occurred for each participant interaction. The new automated nonverbal communication behavior assessment will be programed into the MPathic-VR intervention for quality testing.

A prospective quality check will be conducted to test and refine the new automated nonverbal communication behavior assessment of the MPathic-VR’s ability to capture and assess nonverbal communication using the newly added features. This testing is needed to ensure the virtual human software is assessing clinically meaningful nonverbal behavior. Especially, it will be critical to test whether the system can recognize predefined aspects of nonverbal behavior by comparing system-recorded (Kinect) responses to manually scored records for predefined nonverbal behavior produced by provider test participants (n=30).

All data will be dichotomous (Yes/No) for each nonverbal behavior. Participants will be directed in advance to produce certain behaviors during the scenarios. Then, 2 analysts (principal investigator and research assistant) blinded to the directions will code behavior for each interaction from a video recording using the nonverbal communication behavior assessment, the RIAS, and the FACS. Because the manual recording will be considered the standard, the principal investigator and second independent reader will score manually to account for and investigate variability in manual coding. An interrater reliability analysis of the system-recorded responses with manually scored responses will be conducted. Dyadic data analysis techniques will also be applied to examine recorded nonverbal behaviors.

Based on accepted interrater reliability of SPIs [52,53], κ=0.6 will be considered adequate interrater reliability and κ=0.8 optimal using Cohen statistic [54,55]. Using the most conservative estimate of detecting κ=0.6 and a 2-tailed test of the null hypothesis of 0 agreement, a sample of 30 is needed for 90% power to assess the reliability [55]. If reliability falls below κ=0.6, we have 2 alternative procedures: (1) identify the lowest-performing cue and delete it to improve reliability, or (2) when 1 cue performs poorly, seek new technology, and repeat the analysis with the new technology, and compare to manually-coded assessment data from the MP4 recording. The outcome of this aim will be a refined virtual human software that includes the automated nonverbal communication assessment and initial quality control check data. Aim 3 will be critical to prepare for a subsequent R01 intervention to refine and test the revised virtual human system that contains novel scenarios assessing and automating both nonverbal and verbal communication after action review feedback.

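### The quality check keeps or drops sensor cues on Cohen κ with a 0.6 cut-off, but the direction script sets the prevalence on which κ partly depends, and no present/absent mix is fixed

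*Protocol article*

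**What the plan says.** The point concerns the prospective quality check in the protocol article (Methods, Exploratory Sequential Design, Data Analysis and Integration).

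- **Data.** Every behavior is rated yes or no. The sensor's record is compared with manual scores from video for 30 provider test participants.
- **How presence arises.** "Participants will be directed in advance to produce certain behaviors during the scenarios". Two coders who do not know the directions score the videos.
- **Reference.** The article ranks the two sources: "Because the manual recording will be considered the standard", it says, two readers will score.
- **Criterion.** Cohen κ of 0.6 is adequate and 0.8 optimal. Below 0.6, the team either drops the weakest cue or looks for other technology and repeats the analysis.
- **Sample size.** "Using the most conservative estimate of detecting κ=0.6" and "a 2-tailed test of the null hypothesis of 0 agreement", the article concludes that "a sample of 30 is needed for 90% power to assess the reliability".

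It gives no share of ratings in which a behavior is to be present, describes no direction to withhold a behavior, and links neither the cut-off nor the power to a prevalence.

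**The concern.** For a binary rating, κ depends on the accuracy of the sensor and also on how common the behavior is. In an observational study prevalence is a fact of nature. Here it is a design choice, because providers act to direction. A fixed κ cut-off therefore demands different accuracy from different cues, according to how often each one is scripted.

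Two things are at stake. First, a good cue that is scripted in nearly every interaction may fall below 0.6 and be dropped or replaced. Second, if a behavior is seldom absent, false detections are hardly tested. With 27 of 30 ratings present, specificity rests on 3 ratings.

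The article names the manual coding as the standard, so sensitivity and specificity can be computed from the same two-by-two table. The stated decision does not use them.

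**Working it through.** **Inputs from the article:** n = 30; κ = 0.6 against 0; two-tailed; 90% power; cut-offs 0.6 and 0.8.

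**Assumed, because not stated:** α = 0.05; prevalence from 50% to 95% (results for 5–50% mirror these); sensor sensitivity = specificity = 0.80, 0.90 or 0.95; one rating per participant per behavior; error-free manual coding.

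**1. The stated sample size.** With null variance 1/n,

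n = ((1.960 + 1.282)/0.6)² = 29.19, rounded up to 30.

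Power at 30 is Φ(0.6·√30 − 1.960) = Φ(1.326) = 90.8%. The figure reproduces. Prevalence does not enter this formula.

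**2. Power when prevalence is taken into account.** For common prevalence p and κ = 0.6, the cell probabilities are p² + 0.6p(1−p) for both yes, 0.4p(1−p) for each disagreement, and (1−p)² + 0.6p(1−p) for both no. At p = 0.9 these are 0.864, 0.036, 0.036 and 0.064. All tables with n = 30 were enumerated. κ was tested against its large-sample null standard error, and tables with a constant rating counted as non-rejection.

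| Prevalence | Exact power, n = 30 | Large-sample power | n for 90% (large-sample) |
|---|---|---|---|
| 50% | 93.7% | 95.1% | 25 |
| 70% | 91.9% | 93.5% | 27 |
| 80% | 87.5% | 90.6% | 30 |
| 90% | 76.0% | 83.6% | 38 |
| 95% | 58.0% | 76.1% | 53 |

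**3. κ for a sensor of fixed accuracy.** With accuracy a (sensitivity = specificity), the sensor says yes with probability s = pa + (1−p)(1−a). Observed agreement is a, chance agreement is e = ps + (1−p)(1−s), and κ = (a − e)/(1 − e). For a = 0.90:

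- p = 0.5: s = 0.50, e = 0.500, κ = 0.400/0.500 = 0.80
- p = 0.8: s = 0.74, e = 0.644, κ = 0.256/0.356 = 0.72
- p = 0.9: s = 0.82, e = 0.756, κ = 0.144/0.244 = 0.59

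| Prevalence | a = 0.80 | a = 0.90 | a = 0.95 |
|---|---|---|---|
| 50% | 0.60 | 0.80 | 0.90 |
| 70% | 0.56 | 0.77 | 0.88 |
| 80% | 0.49 | 0.72 | 0.85 |
| 90% | 0.35 | 0.59 | 0.76 |
| 95% | 0.22 | 0.43 | 0.63 |

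A sensor that is right 80% of the time under a balanced script scores about the same (0.60) as one that is right 90% of the time at 90% prevalence (0.59).

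**4. The cut-off in a sample of 30.** With m ratings present and 30 − m absent, correct detections are binomial in each group. The chance that observed κ falls below 0.6 is:

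| Present of 30 | a = 0.80 | a = 0.90 | a = 0.95 |
|---|---|---|---|
| 15 | 39.3% | 2.6% | 0.1% |
| 24 | 71.6% | 17.5% | 2.0% |
| 27 | 89.9% | 42.0% | 9.8% |
| 28 | 96.0% | 61.8% | 22.1% |

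With all 30 present, κ is zero or undefined whatever the sensor does.

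**The case against.** **The article does not set an unbalanced script.** Providers are told to produce certain behaviors, which on its ordinary reading is a subset, and blinding coders to the directions makes most sense if directions differ. Some absences are therefore likely, and a condensed article may leave the script to the full protocol. This stands: a reader might infer that prevalence will be near 100%, but the text does not say so. It does not remove the point, because the article itself states the κ criterion and its consequence.

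**κ still measures the sensor.** A reader might infer that the script alone decides the result. It does not. At 90% prevalence, accuracy of 0.80, 0.90, 0.95 and 0.99 gives κ of 0.35, 0.59, 0.76 and 0.95. Only an all-present or all-absent script makes κ uninformative.

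**The power statement is not wrong.** The sample size of 30 reproduces. A reader might take "Using the most conservative estimate of detecting κ=0.6" as a claim to cover the worst prevalence, but the plain meaning is the lower of the two named benchmarks, 0.6 rather than 0.8.

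**Unit and rule can be read otherwise.** Coding is per interaction and the scenarios are plural, so there may be more than 30 ratings per behavior, clustered within provider. The 0.6 rule may also refer to reliability over all cues, with the weakest then removed, rather than to each cue's own κ. Both readings would change the probabilities in steps 2 and 4. Neither removes the dependence of κ on prevalence in step 3.

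**Other evidence exists.** The same section compares manual coding with the existing sensor data and the assessment with OSCE nonverbal ratings. That broadens the validity evidence but does not test the newly added features.

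A reader might also infer that dyadic analysis of directed behaviors would only return the script. The article does not state the target of that analysis, and it may include undirected behaviors, so nothing is concluded on it.

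**Conclusion.** The concern holds as a weakness in a stated decision rule. It is neither an arithmetic error nor a claim that the check is uninformative. The investigators control prevalence, and the keep, delete or replace decision rests on an index that moves with it. A sensor with sensitivity and specificity of 0.90 goes from the article's optimal level (0.80) to just under its adequate level (0.59) as prevalence goes from 50% to 90%. Its chance of an observed κ below 0.6 goes from about 3% to about 42%.

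The 90% power is roughly right for prevalence of 20–80% and clearly short only near 10/90% or beyond. The size rests on the assumptions listed above: α of 0.05, equal sensitivity and specificity, error-free manual coding, one rating per participant per behavior, and the rule applied cue by cue. This is a small pilot feeding a later study, so the point is a cheap improvement worth making, not a fatal flaw.

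**What to change.** 1. Allocate directions by a prepared list, preferably randomised, so that each behavior is directed as show in about half of the interactions and do-not-show in the rest. Report the mix that the blinded coders actually saw, since providers may not follow every direction.
2. For each cue, report sensitivity and specificity against the manual standard beside κ, and against the directions as a check. Give confidence intervals that allow for clustering if a provider contributes several interactions.
3. Base the keep, delete or replace decision on κ, sensitivity and specificity together, and say whether the 0.6 rule applies to each cue or overall.
4. State that the 90% power assumes roughly balanced prevalence, and state α.

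The cost is a direction list and two extra proportions per cue, with no extra participants or readers. The two proportions will be imprecise: with 15 ratings each and a true value of 0.90, the standard error is √(0.9·0.1/15) = 0.077. That is still better than a specificity from 3 ratings, where it is √(0.9·0.1/3) = 0.173.

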### Ethical Considerations

This study has been approved by the University of Michigan’s institutional review board (HUM00134766). Informed consent will be requested electronically from each participant interested in participating in the study.

### Privacy and Security

Given the large amount of video data that will be used in this study, several steps will be taken to ensure the security of these documents. For example, all data will be stored on University-approved Box and Dropbox secure storage systems using password-protected security and encrypted computers.

## Results

Data collection for this study started in 2019 by accessing secondary data of the MPathic-VR randomized controlled trial data set (210 medical students and 840 video-recordings of interactions) [56]. These data have been analyzed and are expected to be published in 2023. After analyzing these data, recruitment for the qualitative phase of the exploratory sequential design followed in 2021. We expect to complete data analysis for the qualitative phase by July 2023.

## Discussion

### Principal Findings

This study aims to improve providers’ dissemination of health information and related health outcomes for patients through an enhanced conceptual model of patient-centered communication. This study will not only describe core communication functions but also present a directional model of the interrelationships between those components. This conceptual model will be critical to incorporate into the technology to address verbal and nonverbal communication more comprehensively. It is expected that the resulting conceptual model will be able to capture differences in verbal and nonverbal communication behaviors based on the delivery format (eg, in-person or telehealth visits). Finally, the project will build the nonverbal assessment and automated feedback directly into the virtual human simulation for testing. In doing so, we anticipate learners will be able to incorporate the program feedback and improve their nonverbal behaviors.

We expect to find changes across learners interacting with virtual humans on nonverbal behaviors, including those emphasized by the MPathic-VR (eg, eyebrow raise, nodding, and smiling), as well as other facial expressions (eg, furrowed eyebrows, lip corner puller, lower eyelid raise, and oblique eyebrows slight lip press) [57], and head and body orientation (eg, eye gaze toward virtual human, forward lean, and head tilting). Specifically, we would expect to find an increase in the frequency of nonverbal behaviors across learners after repeated interactions with virtual humans. We also anticipate that feedback from the virtual human will contribute to an increased awareness of learners’ nonverbal behaviors. Dissemination of research findings will occur through conferences and articles.

### Limitations

It is important to consider some limitations of this study. First, a team of researchers will be involved in coding a large number of video recordings to analyze learners’ nonverbal behaviors. As a result, coder drift can occur, and discrepancies across coders can arise. To mitigate potential issues of coder drift, the team will meet regularly to discuss any discrepancies throughout the coding process. Second, the role of culture is critical to the assessment of nonverbal behaviors. Nevertheless, a previous study assessing the effectiveness of the MPathic-VR for teaching intercultural and interprofessional communication among medical students demonstrated that the MPathic-VR helped to increase students’ scores after repeated exposure, thus leading to increased awareness of cultural components [36]. Moreover, previous research found significantly higher scores on cultural conversational verbal and nonverbal behaviors for participants exposed to a virtual human condition compared to using illustrations as guides [58]. Thus, the use of virtual humans has been shown to enhance cultural awareness across interactions.

### Conclusions

This research has implications for a wide range of disease areas and broad applicability to medication safety, informed consent processes, patient instructions, and treatment adherence. One of the main strengths of this study is the potential to advance understanding of key aspects of nonverbal communication that can be used to develop informatics-based interventions and ultimately improve patient-provider communication. Using a multistage mixed methods design consisting of convergent and exploratory sequential components, we will be able to more thoroughly understand the nonverbal elements that lead to skill enhancement, develop a model, and automate nonverbal communication behavior assessment. These results will be needed for further virtual human simulation development and will help advance biomedical informatics.

## Appendix

Multimedia Appendix 1 Peer review report from the National Library of Medicine Special Emphasis Panel - Conflict of Interest and Career Awards (National Institutes of Health, USA).

## Abbreviations

FACS: Facial Action Coding System
OSCE: objective structured clinical examination
RIAS: Roter Interaction Analysis System
SPI: standardized patients instructor
